## Abstract

**Background:**

Infectious diseases are among the most common causes of hospitalization in older adults and may lead to a high burden on the individual’s health and healthcare system. However, it is unclear whether and to which extent these events might affect frailty, fastening its development or hampering its reversion. The aims of the INFRAGEN project are 1) to assess the impact of acute infections on frailty trajectories in older inpatients, and 2) to evaluate the modifying effect of sociodemographic, clinical, functional, and genetic/epigenetic factors on that association.

**Methods:**

INFRAGEN is a multicenter prospective observational study that will be conducted in the acute Geriatric Units of four Italian centers (Ferrara, Padova, Monza, and Napoli). The project will involve individuals aged ≥ 70 with no or mild-to-moderate pre-admission frailty (Clinical Frailty Scale [CFS] < 6) and diagnosis of acute infectious diseases at the time of hospital admission or during hospitalization. For each participant, we will record data concerning the multidimensional geriatric assessment and the type and severity of infectious diseases (diagnosed according to ICD-9 codes). Blood samples will be collected to assess Global DNA methylation, Leukocyte Telomere Length (LTL), and levels of circulating markers associated with biological processes related to frailty (inflammatory state, dysmetabolism, brain modifications, and oxidative stress). Frailty status will be evaluated through the CFS and Frailty Index at admission (referring to the 2 weeks before hospitalization), hospital discharge, and after 3 months. In a subsample, genetic/epigenetic analyses will also be performed at the 3-month follow-up.

**Discussion:**

INFRAGEN will contribute to exploring the complex pathophysiologic mechanisms of frailty in the context of infections in older adults through a translational approach.

**Trial registrations:**

NCT06430073 (ClinicalTrials.gov); Registration date: 2024–05-28.

## Background

Frailty, a geriatric syndrome characterized by reduced biological reserves and increased vulnerability to stressors, represents a cornerstone of geriatric clinical practice and research. As the global population ages, this syndrome is expected to constitute an increasingly pressing public health problem. It is associated with several adverse outcomes, including acute and chronic conditions, disability, cognitive decline, and mortality [1, 2].

Frailty exacerbates age-related changes in the immune system and chronic inflammation [3], presumably increasing the individual vulnerability to infections. In turn, infections can trigger inflammatory responses and aggravate the detrimental effects of hospitalization on the individual’s resilience and functional status [4]. Previous studies have shown a link between frailty at hospital admission and adverse outcomes in patients with infectious diseases, including an increased risk of hospital readmission and mortality [5] and poorer medium-term functional trajectories [6]. However, the intricate relationship between frailty and acute infections remains poorly understood, as does the impact of acute infections on this geriatric syndrome.

To date, research focuses mainly on COVID-19 and shows that infection significantly worsens frailty, particularly in hospitalized patients [7] and those with pre-existing frailty [8]. Moreover, studies investigating changes in frailty during hospitalization have generally assessed frailty only at admission, neglecting the pre-admission status and often overlooking the potential impact of infectious diseases [9, 10].

An interesting aspect to consider in the context of the interplay between frailty and infections is the role of genetic and epigenetic biomarkers. Emerging research points to the potential involvement of factors, such as global DNA methylation and telomere length, in the development and progression of frailty [11–13]. However, further studies are necessary to gain a deeper understanding of their roles and potential clinical implications.

The INFRAGEN prospective multicenter study aims to evaluate the impact of infections on changes to frailty in hospitalized older patients, focusing on clinical, biochemical, genetic, and epigenetic markers at hospital admission. Moreover, the study will examine whether changes in frailty over three months are linked to epigenomic DNA modifications in a subgroup of patients.

The specific aims of the study will be: a) to assess the impact of infections—both with and without systemic inflammatory response—on frailty profiles from pre-admission to hospital discharge in older patients with no to mild pre-admission frailty (*primary aim*); b) to examine the link between changes in frailty and genetic/epigenetic markers, such as global DNA methylation and telomere length, exploring whether these biomarkers can predict the course of in-hospital and post-discharge frailty; c) to evaluate the trend of circulating inflammatory and aging-related biomarkers in modulating the impact of infections on frailty progression; and d) to assess the impact of infections on frailty trajectories over a three-month follow-up after discharge, and the modifying role of sociodemographic, clinical and (epi)genetic factors.

While previous research has linked hospitalizations to a decline in physical and cognitive health, leading to frailty in older patients, limited evidence exists on how infections specifically drive these changes. We hypothesize that patients experiencing a higher number and severity of acute infections, especially those with underlying systemic inflammation, may show a steeper functional decline during and after hospitalization. Additionally, we expect that genetic, epigenetic, and clinical factors—such as older age, multimorbidity, polypharmacy, specific DNA methylation and telomere length patterns—may modify the progression of frailty in response to infections.

## Methods/design

### Study design and participants

The INFRAGEN study is a prospective, observational multicenter study involving the Acute Geriatric Units of four Italian centers: S. Anna University Hospital in Ferrara (Emilia-Romagna region, Italy), Padua University Hospital (Veneto region, Italy), IRCCS Foundation San Gerardo dei Tintori in Monza (Lombardy region, Italy), and Federico II University Hospital (Campania region, Italy).

Participants will be selected based on the following criteria: age ≥ 70 years, non-frailty or mild frailty status before admission (CFS < 6), and confirmed diagnosis of acute infectious diseases at the time of hospital admission or during the hospital stay, according to specific ICD-9 codes, with or without a systemic inflammatory response.

Terminally ill patients with an estimated life expectancy of less than 3 months, those with moderate to severe frailty, and individuals who do not wish to participate in the study or complete follow-up assessments will be excluded.

Written informed consent will be obtained from all participants.

### Sample size calculations

Based on previous reports on the topic [10], we estimated that a total sample of at least 340 older adults with acute infections would be sufficient to detect a minimal clinically significant difference in Frailty Index (FI) of at least 0.03 points from the pre-admission status to hospital discharge, with an alpha of 0.05, and a power of 80%.

### Study procedures

Data will be collected using the RedCap platform. The study will include three assessment points (Fig. 1): hospital admission (Time 1), discharge (Time 2), and three months after hospital discharge (Time 3).

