**Fig. 1 Fig1:**
[figure not shown]
Graphical summary of the INFRAGEN study protocol

Time 3 assessment will be performed through an outpatient follow-up visit, home visit, or telephone interview, depending on the centers’ resources and the patient’s characteristics and availability.

Each assessment will include face-to-face interviews, administration of validated scales and questionnaires, physical tests, and blood sampling (the latter only at Time 1 and 3, and limited to the subgroup undergoing outpatient clinic visits).

The data collected from each participant are briefly described below.

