#### Genetic and epigenetic analyses

At Time 1 and Time 3 (only for a subsample of participants), blood samples will be collected and processed for plasma and blood cell stocking for DNA extraction.

DNA extraction from whole blood will be performed by Automated Genomic DNA Purification EZ1 XL machine (QIAGEN).

Global DNA methylation assessment will be performed by “highly quantitative pyrosequencing” technique as genome-wide DNA methylation levels and as gene promoter associated CpG islands utilizing selected age-related methylation marker loci and at LINE-1, Alu, Sat-alpha repetitive elements (as a surrogate for global genome methylation) as previously described [26–28]. Results will be also confirmed by internal Illumina Infinium 450 k beadchip array.

Leukocyte Telomere Length (LTL) will be determined using quantitative real-time PCR (QuantStudio™ 3 System; Applied Biosystems) according to the method of Cawthon [29], the 36B4 will be used as a single copy gene reference (SCR), and the ratio Telomere/36B4 (T/S) will be estimated as indicator of LTL [2 − ∆Ct (△Ct = Ct TL − Ct 36B4)].

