First, the study will quantify the impact of infections on the change in individuals’ frailty status from pre-admission to hospital discharge. Evidence from the SARS-CoV-2 pandemic suggests that infectious diseases can substantially promote frailty development even beyond 3 months of acute illness [7, 8]. However, data on how the most common types of infection, their severity, the occurrence of multiple infectious diseases, and their related level of systemic inflammation may influence the progression of frailty in older adults are lacking. Furthermore, there is some heterogeneity in the definitions of frailty adopted across various studies. Second, the project will explore the interaction between infections and in-hospital frailty status in influencing adverse endpoints, such as in-hospital mortality, length of hospital stay, and discharge destination. For instance, sepsis in frail patients has been shown to worsen mortality compared to non-frail patients [31], and other infections such as pneumonia, COVID-19, or influenza may have similar detrimental impacts [32–34]. Additionally, frailty is linked to a higher risk of urinary tract infections [35]. Third, the project will assess whether global DNA methylation and telomere length patterns at hospital admission are predictors of in-hospital and post-discharge frailty trajectories. In the literature, these epigenomic and genomic markers have been linked to cellular senescence and aging [36]. For example, shorter LTL have been associated with increased risk of infections, various malignant tumors (esophageal cancer, lymphoid and myeloid leukemia), and mortality from cardiovascular, respiratory, digestive, and musculoskeletal diseases and COVID-19 [11]. However, the role of these genomic markers in predicting frailty or functional changes has not been fully investigated [13]. This project will allow us to explore whether DNA methylation and telomere length variations are involved in the pathogenetic processes leading to frailty, especially following an infection. Notably, epigenetic modifications and telomere attrition (dynamic epigenomics) are sensitive to exogenous and endogenous stressors, which strongly relates to an individual’s baseline epigenome and their personal response to stressors, thus accounting for the relationship between epigenomic patterning and developmental trajectories or disease [37]. Although a 3-month period may be a short time interval to detect changes in LTL, we cannot rule a negative impact of infectious diseases and inflammatory processes on this aspect in vulnerable individuals, such as older inpatients. Moreover, blood cells composition of the included participants is expected to change between in-hospital and post-discharge assessments, and this issue may further influence LTL.

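### The first blood sample is fixed at hospital admission although the qualifying infection may begin later, so the inflammatory markers mix pre-infection and during-infection states

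*Protocol article*

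**What the plan says.** Eligibility (Protocol article, Study design and participants) requires a "confirmed diagnosis of acute infectious diseases at the time of hospital admission or during the hospital stay". The Abstract repeats this: "diagnosis of acute infectious diseases at the time of hospital admission or during hospitalization". A patient can therefore qualify through an infection that was absent on arrival.

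The schedule (Study procedures) has three points for every participant: "hospital admission (Time 1), discharge (Time 2), and three months after hospital discharge (Time 3". The text below Fig. 1 describes "blood sampling (the latter only at Time 1 and 3, and limited to the subgroup undergoing outpatient clinic visits". Genetic and epigenetic analyses agrees: "At Time 1 and Time 3 (only for a subsample of participants), blood samples will be collected and processed". No sample is tied to the diagnosis of an infection.

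The markers are described as admission values. The Background presents the study as "focusing on clinical, biochemical, genetic, and epigenetic markers at hospital admission", and the Discussion asks whether "global DNA methylation and telomere length patterns at hospital admission are predictors of in-hospital and post-discharge frailty trajectories".

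Biochemical analyses lists TNF-a, IL6 and CRP among the circulating markers. Infectious disease says that infections arising later in the stay are documented, but links no sample to them. In Statistical analysis, the infection factors named for the models are number, site and severity. Neither onset (at admission or in hospital) nor the interval from infection to sampling is named. Frailty status derives the baseline retrospectively, for everyone, at two weeks before admission.

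**The concern.** Aim c concerns how circulating inflammatory and aging-related markers modulate the impact of infection on frailty. CRP, IL6 and TNF-a respond to infection, so their values depend on whether the patient was infected when sampled. With Time 1 at admission, a patient admitted with pneumonia is sampled during the infection. A patient who develops one on, say, day 8 is sampled before it, during whatever illness led to admission. The two values share a name but measure different things.

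Aim c also speaks of the trend of these markers. Where a Time 3 sample exists, the change from Time 1 runs from during infection to recovery in the first patient, and from before infection to recovery in the second.

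A coefficient estimated over both groups describes neither the response to infection nor the pre-infection state, and it may carry differences between the groups that have nothing to do with the marker. Four centers could also resolve the gap differently when drawing blood, so onset, sampling time and center could become entangled.

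**Working it through.** **1. The statements side by side**

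| Item | What the article fixes | Where |
|---|---|---|
| When the qualifying infection may arise | At admission or later in the stay | Abstract; Study design and participants |
| Time 1 | Hospital admission | Study procedures |
| Blood draws | Time 1 and Time 3 only | Text below Fig. 1; Genetic and epigenetic analyses |
| Meaning of the markers | Values at admission | Background; Discussion |
| Infection factors in the models | Number, site, severity | Statistical analysis |
| Frailty baseline | Two weeks before admission, for all | Frailty status |

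For a first infection that arises during the stay, three readings are open:

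- Blood was drawn at admission. It predates the infection.
- Blood is drawn after diagnosis. It shows the infection but is not Time 1 as defined.
- No first sample is available.

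Under the first reading the marker variable mixes infection states. Under the second the schedule is not followed, and patients are sampled at different points of their stay. Under the third a group of participants has no marker value. The text does not choose between them.

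**2. Illustration of the consequence**

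The documents give the planned total of 340 (Sample size calculations) but no hospital-onset share and no marker shift. Everything else in this step is assumed.

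*Patients affected.* With a hospital-onset share h of 5% to 30%: 0.05 × 340 = 17, and 0.30 × 340 = 102.

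*Share of marker variance due to mixing.* Take unit variance within each group and a mean difference of m SD. The share is h(1−h)m² / [1 + h(1−h)m²].

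- m = 1: 0.0475/1.0475 = 4.5% at h = 5%; 0.21/1.21 = 17% at h = 30%.
- m = 2: 0.19/1.19 = 16% at h = 5%; 0.84/1.84 = 46% at h = 30%.

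*Effect on a slope.* Suppose the slope is 0.3 SD of frailty decline per SD of marker in patients sampled during infection and zero in those sampled before it, the latter have a marker mean 1 SD lower, and they decline d SD more. Then

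pooled slope = [0.3(1−h) − h(1−h)d] / [1 + h(1−h)].

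| h | d = 0 | Loss | d = 0.5 | Loss |
|---|---|---|---|---|
| 10% | 0.27/1.09 = 0.248 | 17% | 0.225/1.09 = 0.206 | 31% |
| 20% | 0.24/1.16 = 0.207 | 31% | 0.16/1.16 = 0.138 | 54% |
| 30% | 0.21/1.21 = 0.174 | 42% | 0.105/1.21 = 0.087 | 71% |

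*Sensitivity to the zero slope.* If the slope is 0.3 in both groups and d = 0, the pooled slope is 0.3/[1 + h(1−h)]: 0.275, 0.259 and 0.248 at 10%, 20% and 30%, a loss of 8%, 14% and 17%. If the slope is 0.3 in both and hospital-onset patients decline 0.5 SD less, then at 20% it is (0.3 + 0.16 × 0.5)/1.16 = 0.328, which is above 0.3. The direction of the bias is therefore not fixed either.

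*Why an onset covariate alone may not be enough.* A main effect for onset removes the between-group terms. With slopes of 0.3 and zero, the common slope is still 0.3(1−h): 0.27, 0.24 and 0.21. Only separate strata or a marker-by-onset interaction recover each group's own slope.

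**The case against.** Several arguments on the other side stand.

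- **Prediction from admission is legitimate.** Aim b asks whether methylation and telomere length predict the course of frailty. A value taken before a later infection can be a valid predictor, and even a valid effect modifier, whereas a post-diagnosis draw may partly reflect the infection itself. A reader might infer that an admission value says nothing about the response to a later infection. The article does not support that.
- **Consent and enrolment are not timed.** The text says only "Written informed consent will be obtained from all participants". A reader might infer that a consented admission sample cannot exist for these patients. Centers might instead consent and sample on arrival and keep those who later qualify; nothing shown confirms or excludes this. Such samples would still predate the infection.
- **The circulating-marker model is not specified.** The detailed marker analysis covers only methylation and telomere length. Pooling of CRP, IL6 and similar markers is inferred from the single Time 1 definition, not stated. The examples of confounders are also an open list.
- **The slope losses are not estimates.** Every input is assumed, the zero slope largely builds in the result, and the formula ignores the planned adjustment for center, comorbidities, length of stay and in-hospital events. Methylation is to be analysed in quartiles, not as a slope per SD.

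It can also be said that Fig. 1 or the full protocol may define a sampling window. That may be so, but the article does not merely leave the window open. It sets Time 1 at admission while admitting infections that arise later, and the two do not fit as written.

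**Conclusion.** The point holds as a conflict between the eligibility rule and the sampling schedule. For hospital-onset infections, the first sample either predates the infection or is not the admission sample that the article defines, and the listed infection factors do not separate these patients from those infected on arrival.

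Its reach is limited. It bears mainly on the inflammatory markers of aim c. It is weaker for methylation and telomere length, although the Discussion itself notes that these respond to stressors and that blood cell composition may influence telomere length. A reader might infer that the primary result is compromised as well. It is not: the change in Frailty Index starts from the same pre-admission reference for every patient.

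No size can be put on the bias. The losses of 17% to 71% follow from assumed shares, slopes and shifts. Other equally open assumptions give 8% to 17%, or a bias in the opposite direction. The conclusion rests only on the stated text and on the premise that some participants qualify through an infection acquired in hospital, which the eligibility rule expressly allows.

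**What to change.** - **Reconcile the text.** Bring Study design and participants into line with Study procedures and Genetic and epigenetic analyses by stating when the first sample is drawn if the qualifying infection arises during the stay. For the inflammatory markers, use a fixed window after diagnosis of that infection. For infections present at admission this is the admission visit.
- **Record two dates.** Enter the date of diagnosis of the qualifying infection and the date of sampling, so that the interval is known.
- **Separate the groups.** In the marker analyses, include onset (at admission or in hospital) as a stratum or a marker-by-onset interaction. Use the admission-onset group as the main population for aim c and as a sensitivity analysis for aim b. Removing hospital-onset patients from the main analysis of aim b is not needed, since a pre-infection value can serve that aim.

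The cost is one or two date fields, a small change in sampling instructions at the four centers, and some loss of precision in the aim c marker analysis. The dates should be collected from the start, because the interval may not be reliably recoverable afterwards.

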**Fig. 1 Fig1:**
[figure not shown]
Graphical summary of the INFRAGEN study protocol

Time 3 assessment will be performed through an outpatient follow-up visit, home visit, or telephone interview, depending on the centers’ resources and the patient’s characteristics and availability.

Each assessment will include face-to-face interviews, administration of validated scales and questionnaires, physical tests, and blood sampling (the latter only at Time 1 and 3, and limited to the subgroup undergoing outpatient clinic visits).

The data collected from each participant are briefly described below.

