The patterns of global DNA methylation will be assessed in duplicate for each sample and expressed in percentage as the mean obtained by the two evaluations and considered valuable with a discrepancy < 2%. Methylation percentages will be stratified into quartiles, and the combined middle two quartiles will be used as the reference category to identify potential correlations at the top or bottom of the distribution with the clinical phenotypes. As a measure of the relative Telomere length, the ratio of the telomere repeat copy number to the number of single-copy genes (T/S ratio) will be determined by quantitative PCR using the single-copy gene 36B4 for reference and a standard curve. Quality controls and assay validation tests will be assessed by official commercially recognized standards (Qiagen, LifeTechnology). The association of global DNA methylation pattern and telomere length with the frailty trajectories will be evaluated through a linear mixed model, adjusted for potential confounders. Appropriate subgroup and interaction analyses will be performed to explore the possible modifying effects by sex, the presence of the most prevalent clinical conditions, and infection-related factors (i.e. number, site, and severity of infections) on the studied associations.

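### The 3-month marker-change analysis uses clinic attenders only and spans a blood-cell shift the article itself predicts; no stated step separates either from frailty change, so its associations may be biased

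*Protocol article*

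**What the plan says.** **Follow-up mode.** Under Study procedures, "Time 3 assessment will be performed through an outpatient follow-up visit, home visit, or telephone interview", with the choice "depending on the centers’ resources and the patient’s characteristics and availability".

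**Who gives blood.** The same section says blood is taken "the latter only at Time 1 and 3, and limited to the subgroup undergoing outpatient clinic visits". The Abstract attaches the subsample to the later time point only: "In a subsample, genetic/epigenetic analyses will also be performed at the 3-month follow-up". The section on genetic and epigenetic analyses also places its subsample note after Time 3.

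**What is measured.** "DNA extraction from whole blood will be performed by" an automated system, so the DNA comes from mixed leukocytes. Participants are enrolled because of an acute infection diagnosed at admission or during the stay.

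**What the article expects.** The Discussion states that "blood cells composition of the included participants is expected to change between in-hospital and post-discharge assessments, and this issue may further influence LTL".

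**Analysis.** "The association of global DNA methylation pattern and telomere length with the frailty trajectories will be evaluated through a linear mixed model", with adjustment for unspecified potential confounders. The example covariates under Statistical analysis, given for the frailty-change model, are sociodemographic data, center, comorbidities, length of stay and in-hospital events not related to the infection. Neither that list nor the description of collected data contains a leukocyte count or differential.

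**Aim affected.** The Background asks whether frailty change over three months is linked to epigenomic change in a subgroup. A separate question, whether admission markers predict later frailty, is set out in the aims and the Discussion.

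**The concern.** Two mechanisms could distort the 3-month marker-change result.

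*Selection.* If patients who have become frailer are more often followed at home or by telephone, the outcome helps decide who has a second marker value. A mixed model that uses every available frailty measurement does not recover a blood sample that was never drawn.

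*Cell mix.* Infection severity plausibly drives both the leukocyte shift and the change in frailty. Whole-blood methylation and telomere length both depend on which cells are present. An apparent marker change that follows frailty could then be no more than the return of the leukocyte profile to normal. The same confounding can reach the admission-marker analyses, because that sample is also whole blood from patients with acute infection.

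At stake is a secondary aim that the article presents as one of its novel contributions. A differential that is not captured near the draw may be hard to add later.

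**Working it through.** The article gives no figure to reproduce here. The sample of 340 is for the primary change in Frailty Index (FI), and the size of the epigenetic subsample is not stated. Every input below is an assumption chosen to show a range.

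**1. Selection when a true association exists.** Let M be standardised marker change and F standardised FI change (higher is worse), with F = 0.30·M + error. Attendance is logistic in F, 50% overall, and its odds fall by a factor of 2, 3 or 5 per SD of worsening. Simulated slope of F on M among attenders (about one million draws):

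| Fall in odds per SD | Slope in attenders | Attenuation | Mean F in attenders |
|---|---|---|---|
| 2 | 0.274 | 1 − 0.274/0.30 = 9% | −0.31 SD |
| 3 | 0.247 | 1 − 0.247/0.30 = 18% | −0.44 SD |
| 5 | 0.217 | 1 − 0.217/0.30 = 28% | −0.55 SD |

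**2. Selection when there is no true association.** If attendance depends on F alone, the correlation among attenders is about 0. If it depends on both F and M, with log-odds of 0.5 to 1.0 per SD for each, the correlation among attenders is about −0.05 to −0.15.

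**3. Which weights correct it.** Same set-up as step 1, with inverse-probability weights from a fitted attendance model. The discharge measure is assumed to correlate 0.5 to 0.7 with 3-month change.

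| Fall in odds per SD | Unweighted | Weighted on discharge measure | Weighted on 3-month FI change |
|---|---|---|---|
| 2 | 0.274 | 0.275–0.279 | about 0.30 |
| 3 | 0.247 | 0.249–0.257 | about 0.30 |
| 5 | 0.217 | 0.218–0.228 | about 0.30 |

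Weights built on discharge status leave almost all of the bias. Weights that include 3-month frailty remove it, and frailty can be obtained by all three contact modes.

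**4. Price of the weights.** With attendance probability 1/(1 + exp(bF)), the weight is 1 + exp(bF). The effective share of the attender sample is then 2/(1 + exp(b²/2)).
- b = ln 2: 2/(1 + 1.27) = 88%
- b = ln 3: 2/(1 + 1.83) = 71%
- b = ln 5: 2/(1 + 3.65) = 43%

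**5. Cell mix.** Suppose the marker has no direct link to frailty, and cell mix correlates r₁ = 0.2 to 0.4 with frailty change and r₂ = 0.2 to 0.6 with the marker. The induced correlation is r = r₁·r₂, from 0.2 × 0.2 = 0.04 to 0.4 × 0.6 = 0.24. With half of 340 sampled (n = 170), the two-sided 5% false-positive rate is Φ(k − 1.96) + Φ(−k − 1.96), where k = atanh(r)·√167.
- r = 0.04: k = 0.52, rate 8%
- r = 0.24: k = 3.16, rate 89%
- r₁ = 0: rate stays at 5%

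In simulation, adjusting for the cell measure returns the correlation to about 0 at every combination.

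**The case against.** **The charge is largely one of silence.** The marker models are adjusted for potential confounders, the covariate list is open, and the article calls its data description brief. A full protocol or analysis plan could contain both leukocyte adjustment and weighting. This stands: the accurate statement is that none is named, not that none will be done. It does not dispose of the point, because the article itself predicts the cell shift and attaches no handling to it.

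**Selection on frailty is inferred.** The article does not say that worsened patients are seen at home. Center resources need not track frailty, and center is a named covariate. This also stands, and is why the conclusion is a risk. Patient characteristics are nevertheless one of the stated determinants.

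**A reader might infer that the whole epigenetic aim is answered only in the least frail survivors.** The documents do not support that. Admission markers can be related to discharge and 3-month frailty without any Time 3 blood, and the change question is openly limited to a subgroup.

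**A reader might also take the sampling sentence to restrict Time 1 blood to later attenders.** Clinic attendance is unknown at admission, and the Abstract ties the subsample to 3 months. This is loose wording, not a design restriction.

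**Adjusting for leukocytes may remove part of the effect of interest.** The shift may lie on the inflammatory pathway the study wants to examine. This stands, and is a reason to report both models rather than let the adjusted one replace the other.

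**Conclusion.** The point holds as a risk of bias in a secondary analysis. Time 3 markers come from a subgroup selected partly on patient characteristics, and the two samples span a cell-composition change that the article foresees without stating how it will be separated from marker change. Attendance selection concerns Time 3 markers only; cell mix may also confound the admission-marker analyses.

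The size cannot be taken from the document. On the assumptions shown, selection attenuates a real slope by 9% to 28% and keeps its sign. Cell mix could induce a correlation of 0.04 to 0.24, or none if it is unrelated to frailty change. It would be tempting to say that the marker–frailty associations simply are selection and cell mix. That goes too far, because under some of the assumptions tried there is no spurious association at all. The primary aim, FI change from pre-admission to discharge, is untouched.

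**What to change.** 1. **Cell composition.** Record the leukocyte differential from the routine blood count nearest each draw, or use array-estimated cell proportions where the array is run. Report every methylation and telomere model with cell-composition adjustment alongside the unadjusted model, and say that the gap between them may be partly confounding and partly pathway.
2. **Attendance.** Weight the Time 3 marker analyses by the inverse probability of clinic attendance among those contacted at 3 months. Put 3-month FI and Clinical Frailty Scale in the weight model, with center, age, function and severity. Do not rely on discharge measures alone.
3. **Wording.** Under Study procedures, state that the clinic restriction applies to Time 3 blood only, in line with the Abstract.

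The cost is one data-form field filled from routine results, some analysis wording, and precision lost to weighting. In the worked example the effective sample falls to 88%, 71% or 43% of attenders as selection strengthens. Weighting represents only patients reached at 3 months; it does not stand in for those who died or were lost before then.
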